**Methods:**

A parallel-group randomised controlled trial will be conducted recruiting participants with a mental health condition through community mental health services and advertisement on social media. Participants will be randomly assigned to receive either a health information pack only (control) or a health information pack and a proactive referral to a free, government-funded telephone coaching service, the NSW Get Healthy Coaching and Information Service® (intervention), which offers up to 13 telephone coaching calls with a University Qualified Health Coach to assist with client-identified goals relating to physical activity, healthy eating, weight management, or alcohol reduction. Data will be collected via telephone surveys at baseline and 6 months post-recruitment. Primary outcomes are as follows: (1) minutes of moderate to vigorous physical activity per week, (2) serves of fruit consumed per day, (3) serves of vegetables consumed per day, and (4) a composite measure assessing attempts to change at least one health risk behaviour (any attempts to change physical activity, fruit consumption, vegetable consumption, or other parts of nutrition). Secondary outcomes include weight and body mass index.

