#### Participant characteristics

*Sociodemographic*: demographic information collected at baseline will include age, gender identity, highest level of education, current employment status, current marital status, and Aboriginal and/or Torres Strait Islander status. *Clinical*: primary and any secondary mental health diagnoses for which the participant is currently receiving or has received treatment for within the past 12 months and any physical health conditions that have required treatment within the past 2 months. These questions will be included in the baseline survey only. Current medications for mental health conditions will be recorded during baseline and follow-up surveys. *Health behaviour risk status*: calculated as per the Australian Guidelines for each health behaviour, with risk defined as follows; tobacco smoking, e.g. “how often did you smoke tobacco products in the last month?” (any use of tobacco products), and from the measures outlined above for alcohol consumption (AUDIT-C) [41, 42], physical activity (SIMPAQ) (< 150 min/week of MVPA) [36], and fruit (< 2 serves daily) and vegetable consumption (< 5 serves) [35].

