### Statistical analysis

Descriptive statistics will be used to describe baseline participant characteristics by group. Analyses will follow intention to treat principles, where participants are analysed according to their randomised treatment allocation. The initial analyses will be undertaken using all participants who provided baseline data. The three primary outcomes that are continuous variables (minutes physical activity, fruit serves, vegetable serves) will be analysed using linear mixed models, including a random intercept and random time effect for participant, as well as fixed effects for treatment group, time, and group*time interaction, and possible confounding variables including age, gender identity, and mental health diagnosis. Similar analyses will be conducted for continuous secondary outcomes (weight, BMI).

The same analyses using logistic mixed models will be conducted for dichotomous primary and secondary outcomes (attempts to change health behaviour variables).

As it is expected that approximately 50% of intervention participants will not enrol with the GHS (Fig. 1), an exploratory ‘per protocol’ analysis will be undertaken based on only those intervention participants who enrolled with the GHS (enrollers analysis). There are no interim analyses planned.

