#### Sample size and power

The study will aim to recruit 675 participants (540 intervention and 135 control following the 4:1 allocation ratio). As per the intention-to-treat analysis, 55% of participants are anticipated to provide follow-up data (*n* = 297 intervention, *n* = 75 control, total 372). This final sample will provide an 80% power to detect a true difference between groups at follow-up of 0.58 serves of vegetables per day (SD = 1.6) [47], 0.47 serves of fruit per day (SD = 1.3) [35], and 109 min of moderate/vigorous physical activity per week (SD = 300) [48].

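### Age, gender identity and diagnosis have no time interaction in the linear mixed models, so for participants with both surveys they leave the group*time effect unadjusted

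*Protocol article*

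**What the plan says.** The Statistical analysis section gives the model for the three continuous primary outcomes term by term. The random part is described as "including a random intercept and random time effect for participant". The fixed part is "fixed effects for treatment group, time, and group*time interaction, and possible confounding variables including age, gender identity, and mental health diagnosis". Weight and BMI are handled similarly, and for the attempt outcomes "The same analyses using logistic mixed models will be conducted for dichotomous primary and secondary outcomes". On the analysis set: "The initial analyses will be undertaken using all participants who provided baseline data".

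There are two occasions: "Data will be collected via telephone surveys at baseline and 6 months post-recruitment". The covariates do not vary over time. Under Participant characteristics, "demographic information collected at baseline will include age, gender identity", and of the sociodemographic and clinical items, including diagnosis, the article says "These questions will be included in the baseline survey only". Under Sample size and power, "55% of participants are anticipated to provide follow-up data", with that one rate applied to both arms.

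The article does not say in so many words that the covariates are main effects only. That is the natural reading of a list that names one interaction and no other.

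**The concern.** With two surveys, group*time is the difference between arms in mean change. A baseline covariate enters that contrast only if its coefficient may differ between baseline and follow-up, and the model as written does not allow this. Calling the variables possible confounders leads a reader to take the treatment effect as adjusted for them.

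Two things are at stake. First, if the arms differ by chance in a covariate that predicts change, the listed adjustment does not correct it and brings no gain in precision. Second, with 45% expected to lack follow-up, suppose that follow-up depends on a covariate differently in the two arms and that the covariate also predicts change. The group*time estimate is then biased, and main effects do not remove the bias.

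**Working it through.** **The plan's own figure.** With 297 and 75 followed up and two-sided alpha 0.05 (assumed; the article does not state it), the detectable difference at 80% power is (1.960 + 0.842) × SD × √(1/297 + 1/75) = 2.802 × 0.1292 × SD = 0.362 SD. This gives 0.58 vegetable serves (SD 1.6), 0.47 fruit serves (SD 1.3) and 109 min (SD 300), as stated. Computed power is 80.1%, 79.9% and 80.3%. The point below does not touch these figures.

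**Algebra.** Let G be group and X a baseline covariate.

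- Baseline mean: b0 + b1·G + c·X.
- Follow-up mean: b0 + b1·G + b2 + b3·G + c·X.
- Mean change: b2 + b3·G. The c·X term has gone.

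For participants with both surveys, the estimate of b3 is the raw difference in mean change, whether or not X is in the model. With a term d·X·time, mean change becomes b2 + b3·G + d·X, and b3 is adjusted for X.

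**Numerical check.** Simulated data: 540 v 135, SD 1.6, within-person correlation 0.5 (assumed). The covariance was an unstructured 2×2 matrix, equivalent to random intercept plus random time on two occasions.

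| Data | No covariates | Main effects | With covariate*time |
|---|---|---|---|
| Complete | -0.065646 (SE 0.15602) | -0.065646 (SE 0.15602) | -0.0863 (SE 0.1519) |
| With dropout, completers only | -0.12390 | -0.12390 | -0.1467 |
| Same data, baseline-only participants kept | -0.1698 | -0.1437 | -0.1682 |

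The first two rows show exact cancellation. The third is the planned analysis set, where the covariates do move the estimate. On complete data the precision gain from the interaction is 1 - 0.1519/0.15602 = 2.6%. A second simulated data set, fitted with a random intercept only, gave SE 0.0998 falling to 0.0978, or 2.0%.

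**Size under dropout.** Among completers the bias is approximately d × (mean of X in intervention completers minus mean of X in control completers). Take these assumed values: 40% of participants have a diagnosis whose change is 0.5 SD worse; intervention follow-up is 40% in that group and 65% in the rest; control follow-up is 55% throughout; the true effect is 0.

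- Intervention follow-up: 0.4 × 0.40 + 0.6 × 0.65 = 0.16 + 0.39 = 0.55, matching the plan.
- Share with the diagnosis among intervention completers: 0.16/0.55 = 0.291, against 0.400 in control.
- Completer bias: -0.5 × (0.291 - 0.400) = +0.055 SD.

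Keeping baseline-only participants and fitting covariate main effects gave +0.043 SD with a random intercept only (200 replicates, Monte Carlo SE 0.008) and about 0.05 SD (0.08 vegetable serves) with the unstructured covariance, in a scenario based on the same dropout assumptions. With covariate*time terms the corresponding figures were -0.004 SD and about 0.01 serves. On the outcome scales, 0.043 SD is 0.07 vegetable serves or 13 min of activity per week. As shares of 0.362 SD, 0.043 is 12% and 0.05 is 14%.

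**Range over other assumptions.** Bias in vegetable serves, true value 0, SE about 0.20, 300 simulations each, unstructured covariance. X is binary with prevalence 50%; follow-up is given for X=0 / X=1.

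| Follow-up, control; intervention | Effect of X, baseline then follow-up | None | Main effects | With covariate*time |
|---|---|---|---|---|
| 65/45%; 55/55% | 1.0 then 0.2 | -0.02 | -0.05 | 0.01 |
| 75/35%; 35/75% | 1.0 then 0.2 | -0.10 | -0.26 | -0.01 |
| 75/35%; 35/75% | 0 then 0.8 | 0.28 | 0.24 | -0.02 |
| 75/35%; 35/75% | 1.0 then 1.0 | 0.17 | 0.00 | 0.01 |
| 75/35%; 75/35% | either 1.0 then 1.0 or 1.0 then 0.2 | within 0.01 of 0 | within 0.01 of 0 | within 0.01 of 0 |

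**Logistic models.** In five complete data sets fitted with a random intercept, adding main effects changed the group*time log odds ratio by 0.001 to 0.013 (for example 0.5146 v 0.5103, and 0.2272 v 0.2402). The cancellation is close but not exact.

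**The case against.** A reader might infer that the covariates do nothing in the planned analysis. The documents do not support that. Participants with baseline data only are retained, and on that set main effects moved the estimate from -0.1698 to -0.1437. The identity holds only for participants with both surveys, and exactly only in the linear models.

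A reader might also infer that main effects never deal with covariate-related dropout. That is wrong too. Where the covariate effect was constant over time, main effects took the bias from 0.17 to 0.00, and where dropout followed the same pattern in both arms there was no bias to correct. Failure needs two conditions together: dropout related to the covariate differently by arm, and a covariate that predicts change. The article predicts neither, and nowhere presents these variables as a remedy for missing data.

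Further, randomisation makes the complete-data group*time effect unbiased in expectation without any covariate. The bias figures rest on assumed values: 0.05 SD is about 0.4 of a standard error (0.129 SD for 297 v 75), and the largest biases need strong dropout patterns reversed between arms. Main effects only is an inference from a condensed article, and a fuller analysis plan could specify otherwise.

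All of this stands and limits the point. It does not remove it. The article lists its model terms and names its one interaction, so this is a stated specification and not a detail left open. Different dropout mechanisms by arm are also conceivable, since only intervention participants receive coaching calls and are contacted again after passive withdrawal (Data collection procedures and measures). That such differences would follow diagnosis is conjecture.

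**Conclusion.** The point holds in limited form. As written, the covariates leave group*time and its standard error unchanged for participants with both surveys in the linear models, which cover three of the four primary outcomes. They neither correct chance imbalance in a covariate that predicts change nor protect against dropout that depends on that covariate differently by arm. Under the assumed moderate pattern the residual bias is about 0.04 to 0.05 SD. It was 0.03 SD (0.05/1.6) under a milder pattern and up to 0.16 SD (0.26/1.6) under an extreme one.

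These figures show what could happen under assumed values; they do not forecast the trial's bias. The document does not support saying that the primary results will be biased or that the adjustment is void. The point concerns the form of the model only.

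**What to change.** State that each named baseline covariate enters the linear mixed models together with its interaction with time, so that it can act on the follow-up mean separately from the baseline mean. An alternative with the same purpose is to model the follow-up value given the baseline value and these covariates. Use the same specification in the logistic mixed models for consistency, and for any other baseline factor added later.

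The change takes one sentence in the Statistical analysis section and a few degrees of freedom. It needs no further data or participants and should be settled before the outcome data are analysed.

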#### Community mental health services

Nine participating community mental health services across two local health districts in NSW will be asked to participate.

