### Randomisation

A computer-generated random allocation sequence will be created by a statistician independent of the project to randomly allocate participants in a 4:1 ratio to the intervention and control groups respectively. The allocation sequence will use permuted-block randomisation with block sizes of 5, 10, and 15. A separate permuted-block schedule will be developed for each community mental health service and for those recruited through advertising. The allocation ratio will be used to account for participants that do not enrol in the GHS. The statistician will upload the random allocation sequence into REDCap (Research Electronic Data Capture) [33, 34]. The software embeds the sequence for use in the randomisation process; however, this is unable to be viewed or downloaded and therefore ensures concealment of allocation to the researchers until participants are assigned to treatment groups (control or intervention). At the end of the baseline survey, CATI interviewers will click the randomisation button in REDCap. Instructions will appear on the screen for CATI interviewers to ensure the participant is not informed of their group allocation.

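### Randomisation is stratified by service and by the advertising stream, but the analysis model does not name the strata; the cost is small and in the conservative direction for the linear models, and naming them is cheap

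*Protocol article*

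**What the plan says.** Randomisation section: "The allocation sequence will use permuted-block randomisation with block sizes of 5, 10, and 15", and "A separate permuted-block schedule will be developed for each community mental health service and for those recruited through advertising". The section on community mental health services adds "Nine participating community mental health services across two local health districts in NSW will be asked to participate". Nine services and one advertising stream make ten strata if all nine take part.

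Statistical analysis section: the continuous primary outcomes go into linear mixed models "including a random intercept and random time effect for participant", with "fixed effects for treatment group, time, and group*time interaction" and "possible confounding variables including age, gender identity, and mental health diagnosis". Weight and BMI are handled similarly. For the attempts outcomes, "The same analyses using logistic mixed models will be conducted for dichotomous primary and secondary outcomes".

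Neither service nor recruitment stream appears in that section as a fixed or a random effect. None of the three named covariates is a stratification factor.

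**The concern.** The usual rule is to analyse as randomised. Blocking within strata balances the arms on whatever the strata predict. A model that leaves the strata out still counts that variation as noise, so its standard error can be too large and its test conservative.

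The article gives some reason to think the strata differ. Clients of the services are screened by service staff, sent a letter and telephoned unless they opt out. Advertising recruits put themselves forward through an online form. That stream was added after registration, and the second Trial status section links the added sites and methods to COVID-19, so stratum is also tied to calendar period.

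Missing data are the second issue. Only 55% are expected to give follow-up data, while the initial analyses use everyone with baseline data. A likelihood analysis of that kind relies on dropout being ignorable given what is in the model, and stratum is a natural variable to condition on.

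**Working it through.** **The plan's own figure.** The planned total is given as "The study will aim to recruit 675 participants (540 intervention and 135 control following the 4:1 allocation ratio"). At 55% follow-up, 540 × 0.55 = 297 and 135 × 0.55 = 74.25 (stated as 75). For vegetables the standard error is 1.6 × √(1/75 + 1/297) = 0.207 and 0.58/0.207 = 2.805. Power is Φ(2.805 − 1.96) = 80.1%, taking two-sided 5% because the article states no significance level. Fruit gives 79.9% and physical activity 80.3%. The stated 80% reproduces. It is a follow-up comparison without strata, and this point does not depend on it.

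**Size of the loss for the group-by-time contrast.** Inputs:
- follow-up fraction f = 0.55 (Sample size and power section), taken as random;
- share of variance between strata ρ = 0.05 or 0.10 (assumed; the article gives none);
- within-person correlation inside strata r = 0.5 (assumed);
- equal variances at both times, a free two-by-two covariance for the two time points, and arms balanced within strata.

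For total variance 1, the likelihood estimate of a group's mean change has variance proportional to V(r) = (1 − r²)/f + (1 − r)². The second term comes from the baseline records, which everyone supplies.

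*Strata in the model:* (1 − ρ) × V(0.5), where V(0.5) = 0.75/0.55 + 0.25 = 1.6136.
- ρ = 0.05: 1.533
- ρ = 0.10: 1.452

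*Strata omitted, same stratum effect at both times (stable level):* the correlation seen by the model rises to ρ + (1 − ρ)r.
- ρ = 0.05: V(0.525) = 1.543; SE ratio √(1.543/1.533) = 1.003
- ρ = 0.10: V(0.55) = 1.471; SE ratio √(1.471/1.452) = 1.006

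*Strata omitted, unrelated stratum effects at the two times (strata drive change):* the correlation seen by the model falls to (1 − ρ)r.
- ρ = 0.05: V(0.475) = 1.684; SE ratio √(1.684/1.533) = 1.048
- ρ = 0.10: V(0.45) = 1.7525; SE ratio √(1.7525/1.452) = 1.099

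**Simulation check.** The set-up was ten strata (assumed sizes nine of 50 and one of 225), blocks of 5, 10 and 15, 4:1 allocation, random 55% follow-up, a two-time-point likelihood analysis and 4,000 runs per setting.
- Stable strata: SE ratio between 0.996 and 1.001, type I error 5.1% to 5.7% without strata. There is no conservatism.
- Strata driving change, r = 0.5: SE ratio about 1.04 (ρ = 0.05) and 1.09 (ρ = 0.10); type I error without strata about 4.0% and 3.2%. Monte Carlo error is about 0.35 points.

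The change scenario is sensitive to r. At r = 0.7 the same formula gives 1.08 and 1.16, while the stable scenario stays below 1.005.

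**The case against.** **The list is open.** The covariates are called possible confounders and introduced as examples. A reader might infer that the model adjusts only for these three and that the strata are ignored. The text supports less: the strata are not named. They are not excluded, and an analysis plan that is not shown may include them. What remains is that the article does name the random effects, the fixed effects and three covariates, yet leaves out the factors that its own randomisation was built on.

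**A simple formula overstates the certainty of the loss.** A reader might apply the textbook result for an unadjusted comparison at follow-up. The standard error is then inflated by 1/√(1 − ρ), which is 2.6% at ρ = 0.05 and 5.4% at 0.10, with actual type I error of 4.4% and 3.9%. That is not the stated model. With a baseline measurement, a participant effect and a group-by-time term, stable differences between strata largely cancel. Contrasts between clinic clients and volunteers are mainly differences in level, so the near-zero case is quite possible. This objection stands, and it is why the size is given as a range starting near zero.

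**The dropout argument has no figures behind it.** Nothing in the article shows that site or stream predicts loss to follow-up, and the likelihood analysis already conditions on the baseline outcome as well as the covariates. This stands as a limit on size. It does not remove the reason for conditioning on a known design factor.

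**Full adjustment everywhere is too much.** About 75 follow-up controls over ten strata is 75/10 = 7.5 per stratum on average. Stratum and stratum-by-time terms in every logistic mixed model would risk empty cells and non-convergence. This is accepted in the fix.

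**Conclusion.** The mismatch between the Randomisation and Statistical analysis sections is real, and its consequence is modest. It does not threaten the validity of the randomisation or of the intention-to-treat comparison, and the article does not support reading it that way. In the linear models any error is towards conservatism. The standard error is essentially unaffected if strata differ only in stable level. It is roughly 4% to 10% too large if strata explaining 5% to 10% of the variance drive change. Those variance shares, the within-person correlation of 0.5, the stratum sizes and random follow-up are all assumptions. If strata explain nothing, nothing is lost.

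The statement about direction is for the linear models. In the logistic models, omitting a prognostic stratum can also pull the conditional odds ratio towards 1. The benefit for the missing-data assumption is a matter of plausibility and cannot be quantified from the document.

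**What to change.** State the stratum terms in the Statistical analysis section before any outcome data are analysed:
- **Linear mixed models** (physical activity, fruit, vegetables, weight, BMI): add randomisation stratum (each service, or advertising) and stratum-by-time as fixed effects.
- **Logistic mixed models** (attempts outcomes): use a sparser form, such as a recruitment-stream indicator plus a random service effect, or services collapsed by health district under a rule fixed before analysis.
- Keep age, gender identity and mental health diagnosis in both.

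The cost is a few sentences. The schedules were built by stratum, so the variable should already be to hand. With ten strata the linear models gain up to 9 + 9 = 18 parameters, against 372 expected follow-up records. Some convergence risk remains in the logistic models even in the sparser form, so the fallback should be written down too. Recruitment need not change. Fixing the terms in advance also removes a later choice, made with the data in view, about whether to adjust.

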### Blinding

Described above, the REDCap randomisation sequence ensures researchers and data collectors remain blinded to the allocation sequence until the baseline survey is complete [29, 30]. Whilst telephone interviewers will not directly state the allocation to the participant, they will inform intervention participants that they will be referred to the GHS. Due to the nature of the intervention, it is not possible for participants to be blinded to their allocation thereafter. When completing the follow-up data collection, telephone interviewers will not be informed of participants’ group allocation until the final section of the survey which includes questions for intervention participants about uptake of the GHS. Blinding before this point cannot be assured as participants may disclose their allocation by mentioning their experience with the service.

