#### Intervention condition

Intervention participants will be sent the same health information pack as the control group and the research team will provide the contact details to the GHS (proactive referral) using the GHS online referral form. In line with standard practice of the GHS, participants will then be contacted by the GHS by telephone to discuss the programs offered and determine if the client would like to enrol. Participants can choose to enrol in the coaching program or the Brief Intervention program, although only approximately 7% of clients chose this option [29]. Participants agreeing to either of these options will be considered to have enrolled with the GHS.

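### The exploratory enrollers analysis is not a randomised comparison and can be biased; a complier estimate should be added and the enrollers contrast reported as descriptive

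*Protocol article*

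**What the plan says.** All references are to the protocol article.

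- **Main analysis (Statistical analysis).** "Analyses will follow intention to treat principles, where participants are analysed according to their randomised treatment allocation". The set is broad: "The initial analyses will be undertaken using all participants who provided baseline data".
- **Enrollers analysis (same section).** The reason given is "As it is expected that approximately 50% of intervention participants will not enrol with the GHS". The response is an analysis labelled exploratory and 'per protocol': "analysis will be undertaken based on only those intervention participants who enrolled with the GHS (enrollers analysis". The control arm is not mentioned, so by implication all controls are the comparator.
- **Model (same section).** Mixed models with group, time and their interaction, plus "possible confounding variables including age, gender identity, and mental health diagnosis".
- **Enrolment (Intervention condition).** After referral the GHS telephones the participant to describe the programs and "determine if the client would like to enrol". The choice is between the coaching program and the Brief Intervention: "Participants agreeing to either of these options will be considered to have enrolled with the GHS".
- **Measurement of uptake (Blinding; Data collection procedures and measures).** Interviewers learn the allocation only at "the final section of the survey which includes questions for intervention participants about uptake of the GHS". The monthly GHS reports also cover intervention participants only.

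**The concern.** The analysis removes part of one randomised arm by a choice made after randomisation and removes nobody from the other. Controls still include people who would have declined the GHS. Any difference in outcome between would-be enrollers and would-be non-enrollers that exists without coaching is then read as an effect of coaching.

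The named covariates do not cover the obvious reason for such a difference. Interest and confidence to change are collected at baseline (Interest and confidence to change health behaviours) but are not named in the model. The outcome most exposed is the composite of any attempt to change, since agreeing to coaching is itself a sign of intent.

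The stake is the reading of a secondary question. Non-enrolment shaped the design: the Randomisation section gives it as the reason for the 4:1 ratio. A reader who wants to know whether coaching works for those who take it up may well turn to this result, and the 'per protocol' label carries no warning about selection.

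**Working it through.** **Inputs.** From Sample size and power: 297 intervention and 75 control participants at follow-up; SDs of 1.6 vegetable serves, 1.3 fruit serves and 300 min/week; differences of 0.58, 0.47 and 109; power 80%. From Statistical analysis: enrolment share π of about 0.5. Assumed, because the article does not give them: two-sided 5% significance, the same π among those followed up, and the gap g, meaning the untreated difference between would-be enrollers and would-be non-enrollers in SD units.

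**1. The plan's own figure.** 540 × 0.55 = 297 and 135 × 0.55 = 74.25 (stated as 75). The standard error (SE) is √(1/75 + 1/297) = 0.129 SD. The detectable difference at 80% power is 0.129 × (1.960 + 0.842) = 0.362 SD, which is 0.58 vegetable serves, 0.47 fruit serves and 109 min. The stated figures are reproduced (power 80.1%, 79.9% and 80.3%).

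**2. Bias of the enrollers contrast.** Enrollers have untreated mean E and non-enrollers N, with g = E − N. Controls average πE + (1 − π)N. With no coaching effect the contrast is E − [πE + (1 − π)N] = (1 − π)g. At π = 0.5 this is half the gap.

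**3. Numbers.** Half of 297 is about 148 enrollers against 75 controls, so SE = √(1/148 + 1/75) = 0.142 SD. For g = 0.3 the bias is 0.15 SD, and 0.15 / 0.1417 = 1.06. The two-sided rejection rate with no true effect is [1 − Φ(1.96 − 1.06)] + Φ(−1.96 − 1.06) = 18.5%.

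| Assumed gap (SD) | Bias, vegetables (serves/day) | Bias, activity (min/week) | False positives, unadjusted follow-up means |
|---|---|---|---|
| 0 | 0 | 0 | 5% |
| 0.1 | 0.08 | 15 | 6.4% |
| 0.2 | 0.16 | 30 | 10.9% |
| 0.3 | 0.24 | 45 | 18.5% |
| 0.5 | 0.40 | 75 | 42% |
| −0.3 | −0.24 | −45 | 18.5% (against the intervention) |

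At g = 0.3 the bias is 0.24/0.58 = 41% of the planned vegetable difference. A simulation of 10,000 trials per scenario agreed: 18.3% rejection at 0.3 SD and 5.1% at zero. Intention to treat stayed at 4.8% to 5.5%, and the CACE stayed centred on zero.

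**4. Sensitivity to enrolment.** If 80% of respondents enrolled, the vegetable bias at g = 0.3 falls to 0.2 × 0.3 × 1.6 = 0.10 serves.

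**5. What a complier estimate would give.** With no control uptake, CACE = intention-to-treat difference / π. At π = 0.5 the differences of 0.58, 0.47 and 109 correspond to 1.16, 0.94 and 218 among enrollers. The vegetable SE goes from 0.21 to 0.41. Estimate and SE double together, so power stays at about 80%. If 5% of controls used the GHS (assumption), the divisor becomes 0.50 − 0.05 = 0.45 and the multiplier 2.22 instead of 2.0.

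**The case against.** The strongest answer is that the article calls this analysis exploratory, makes intention to treat the governing principle and powers the trial on it. That stands: no main conclusion rests on the enrollers contrast.

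A reader might infer that the analysis produces a spurious benefit. The documents do not support that. They give no enroller/non-enroller gap; with a gap of zero there is no bias, and with a negative gap the bias runs against the intervention. Eligibility in both arms already requires willingness to be contacted by a telephone support service, which may narrow the gap. Upward bias is the more plausible direction, not an established one.

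The error rates above also come from unadjusted follow-up means. The planned group-by-time contrast removes stable differences in level, so only a gap in untreated change biases it. The rates illustrate the risk and do not describe the planned model.

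A reader might further infer that a CACE should simply replace the enrollers analysis. It has its own assumption: referral without enrolment must have no effect. The information pack goes to both arms and does not threaten this. The GHS call made before the participant decides could, above all for the attempts outcome. A CACE fitted to respondents is also exposed to the anticipated 45% loss to follow-up. It is the better-founded estimate, but not assumption-free.

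Finally, substantial GHS use by controls is not shown. The article excludes use in the past 4 months and tells controls about self-referral only after the follow-up survey. What stands is that the service is free and open to the public and that control use is not planned to be measured. An unseen analysis plan may add detail, but the restriction to enrolled intervention participants is fixed in the article itself.

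**Conclusion.** The point holds as a moderate one. The enrollers analysis restricts one arm by a self-chosen event after randomisation, so it is not a randomised comparison, and the named covariates do not address motivation. Its bias is (1 − π) times the untreated gap in whatever contrast is analysed. Under an assumed gap of 0.3 SD that survives baseline adjustment, and 50% enrolment among respondents, that is 0.15 SD: 0.24 vegetable serves, 0.20 fruit serves (0.15 × 1.3) or 45 minutes of activity per week. The bias is smaller if more of the respondents enrolled, and absent if there is no gap. That all controls form the comparator is inferred from the wording. Nothing here weakens the intention-to-treat result.

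**What to change.** 1. Add a CACE analysis as the main exploratory estimate of the effect among enrollers. Use randomised arm as the instrument, GHS enrolment as treatment received, and the planned covariates plus the baseline value of the outcome. For the binary attempts outcome, state that the estimate is on the risk-difference scale.
2. State the exclusion restriction openly: referral and the GHS enrolment call have no effect on people who do not enrol. Note that it is least secure for the attempts outcome.
3. Keep the enrollers contrast only as a descriptive, non-randomised comparison, say that all controls are the comparator, and drop the 'per protocol' label.
4. Ask control participants the GHS-uptake question in the final section of the follow-up survey, after the outcome questions. Do not send control details to the GHS for matching: the Data management section tells participants that contact details go to the GHS for the intervention arm only.

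The cost is a change of analysis wording and one extra survey item for controls at the follow-ups still to be done. The CACE standard error is about twice the intention-to-treat standard error at 50% enrolment, and the analysis adds no power.
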